### 4.2. Randomization

Patients will be randomly assigned to Arm A (per os therapy), Arm B (per os therapy and walking), or Arm C (per os therapy and special exercise) in a 1:1:1 ratio by an internet-based distant third-party statistician blinded to the study and participant details. The recruiting physician will be trained and provided with detailed instructions on the recruitment protocol. The objective of randomization is to eliminate selection bias. The trial design is summarized in Figure 1.

### 4.3. Treatments of Adverse Events

Local investigators will handle any adverse events in accordance with current good clinical practice guidelines. Each adverse event will be documented in a case report form, detailing its nature, onset and resolution times, severity, treatment, and outcome. Follow-up examinations will be conducted as needed to ensure patient safety.

Should the monitoring physician observe any harm to a participant or signs of ineffectiveness during the trial, the participant will be removed from the study.

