### 2.5. Statistical Methods

Descriptively, we intend to calculate the mean, standard deviation, minimum, maximum, and range of data, while the occurrence of spontaneous pregnancy will be presented as a percentage. For the evaluation of results, after conducting the Shapiro–Wilk normality test, paired T-tests or Wilcoxon tests will be used to compare baseline and three-month laboratory results within each group, and one-way analysis of variance (ANOVA) or Kruskal–Wallis’s test, along with Tukey’s post hoc test, will be used for comparison among the three groups. Chi-square tests or Fisher’s exact tests are planned to be applied for comparing the numbers or percentages between groups.

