### 4.4. Criteria for Discontinuation of Trial Treatment

The criteria for the discontinuation of a trial are as follows:

(1) The participant refuses further participation or withdraws consent; (2) termination of the entire study; (3) occurrence of a spontaneous pregnancy; (4) failure to adhere to the study rules; (5) attendance of fewer than 75% of the exercise sessions by the participant in the intervention group; (6) occurrence of any other intervention or surgery during the study period that may alter the study outcome; (7) undesirable events related to the treatment, such as acute pain, musculoskeletal complaints, or acute mental or physical trauma preventing continuation of the study; (8) presence of a newly diagnosed malignancy; (9) any situation where oral therapy or physiotherapy is deemed unfit to continue according to the decision of the physician and physiotherapist.

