### 4.7. Efficacy Assessments

The efficacy of the trial treatment will be evaluated using a comprehensive set of parameters measured at the 3-month follow-up. Participants’ weight, height, and BMI will be recorded. This will help in assessing any changes in body composition resulting from the intervention. The regularity and characteristics of participants’ menstrual cycles will be monitored from the start to the end of the study. This continuous observation aims to identify any improvements or alterations in menstrual health. Hormonal evaluations, including levels of AMH, FSH, LH, E2, PRL, TSH, and 25-OH-D3 vitamin, will be conducted at the conclusion of the study as well. As a primary outcome, the change in FSH and AMH levels will be administered. The measurement of progesterone will help evaluate the sufficiency of the luteal phase, which is critical for reproductive health. These measures will provide insights into the hormonal balance and ovarian function of the participants. The FSFI questionnaire will be administered to assess changes in sexual function. This self-reported measure will provide valuable data on the impact of the intervention on participants’ sexual health. The occurrence of spontaneous pregnancy during the study period will be recorded as a primary outcome measure. This will directly indicate the effectiveness of the intervention in improving fertility. These comprehensive assessments will collectively provide a thorough evaluation of the intervention’s efficacy.

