## Figures and Tables

**Figure 1 life-15-00018-f001:**
[figure not shown]
Trial design.

**Table 1 life-15-00018-t001:** Study Assessments and Procedures.

	Screening	Baseline (2–4. Day of Menstrual Cycle)	Baseline (21–22. Day of the Same Cycle)	3 Months (2–4. Day of Cycle)	3 Months (21–22. Day of the Same Cycle)
Assessment					
Investigator meetings	✓				
Informed consent	✓				
Demographics, medical, and family history	✓				
Body composition assessment (Weigh, Height, BMI)	✓			✓	
Menstrual cycle	✓			✓	
Hormone levels (AMH, FSH, LH, E2, PRL, TSH, 25-OH-D3 vitamin)		✓		✓	
Progesteron		✓	✓		✓
FSFI questionnaire		✓		✓	
Spontaneous pregnancy				✓	

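### Section 4.3 takes a woman out of the study for any harm, on wider terms than Section 4.4, and so forfeits her only post-baseline AMH and FSH sample

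*Protocol article*

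**What the plan says.** Section 4.3 (Treatments of Adverse Events) opens its last sentence with "Should the monitoring physician observe any harm to a participant" and ends it with "the participant will be removed from the study". The same sentence has a second trigger, lack of effect, which is not considered here. Section 4.3 also provides for each event to be documented and for safety examinations as needed.

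Section 4.4 (Criteria for Discontinuation of Trial Treatment) covers overlapping ground. Item (7) lists "undesirable events related to the treatment, such as acute pain, musculoskeletal complaints, or acute mental or physical trauma preventing continuation of the study". Item (9) covers "any situation where oral therapy or physiotherapy is deemed unfit to continue according to the decision of the physician and physiotherapist". Its heading refers to treatment, but its lead sentence reads "The criteria for the discontinuation of a trial are as follows".

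The hormonal primary outcome in Section 2.3.1 is the change in FSH and AMH. Section 4.7 places efficacy parameters as "measured at the 3-month follow-up". In Table 1 the row "Hormone levels (AMH, FSH, LH, E2, PRL, TSH, 25-OH-D3 vitamin") is ticked at baseline and at 3 months, both on cycle days 2–4, and nowhere else. Under Section 2.5, paired tests "will be used to compare baseline and three-month laboratory results within each group", and ANOVA or Kruskal–Wallis compares the three groups.

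**The concern.** Two adjacent sections give different rules for the same event. A minor injury unrelated to treatment that leaves a woman fit to continue meets the wording of 4.3 but neither 4.4(7) nor 4.4(9). Under 4.3 she leaves the study, not just the treatment.

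With one post-baseline hormone sample per woman, leaving before month 3 means no primary hormonal value. The analysis plan can say how to handle a missing value, but it cannot recover a sample that was never drawn.

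The loss occurs after randomisation, in an open-label trial, for a reason that treatment can cause. The rule applies in all arms, including for supplement reactions. It may act more often in Arm C, which adds strengthening and stretching to the common oral therapy. That is an inference, because the documents report no event rates.

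**Working it through.** **1. The two rules side by side**

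| | Section 4.3 | Section 4.4(7) | Section 4.4(9) |
|---|---|---|---|
| Trigger | any harm | event related to treatment | oral therapy or physiotherapy unfit to continue |
| Who decides | monitoring physician | not stated | physician and physiotherapist |
| Consequence | leaves the study | heading: trial treatment; lead sentence: a trial | same as item (7) |
| 3-month AMH/FSH kept? | only safety examinations are named | not stated | not stated |

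In item (7), the closing words about preventing continuation may qualify only the trauma or the whole list. The mismatch with 4.3 exists on either reading, because 4.3 does not require relatedness.

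**2. The plan's own figures (Section 2.4)**

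Inputs: f = 0.4, alpha = 0.05, power = 0.95, three equal groups, 15% dropout.

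- Noncentrality for N = 102: λ = N × f² = 102 × 0.16 = 16.32, with 2 and 99 degrees of freedom. Power is 0.955. N = 99 gives 0.949, so 102 is the smallest balanced total that reaches 0.95.
- Inflation: 34 / 0.85 = 40 per arm, 120 in total.

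Both figures reproduce. The loss allowance is 40 − 34 = 6 per arm, shared by every reason for loss. One removal is 1/40 = 2.5% of an arm.

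**3. Power**

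Take A and B at 34 and C at 32, two below the planned number, with the true means fixed at f = 0.4 under equal weights. The noncentrality is λ = Σ nᵢ(μᵢ − μ̄)², where μ̄ is the mean weighted by group size.

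| Pattern of means | λ | Power |
|---|---|---|
| C differs from A and B | 15.67 | 0.947 |
| Linear across the arms | 15.83 | 0.949 |
| A differs from B and C | 16.16 | 0.953 |

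Against 0.955 for 34/34/34, the loss is below 0.01. If A and B lost no one and C lost its full six (40/40/34), power would be 0.964 to 0.976 over the same patterns. Power is not the issue.

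**4. Selection**

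Let k of the 40 women in an arm be removed, and let δ be the mean change in retained women minus the mean change in removed women, in SD units. The full-arm mean is the retained mean minus (k/40) × δ, so analysing only the retained women shifts the arm mean by

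shift = (k/40) × δ.

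For scale, when one arm differs from the other two, f = 0.4 implies d = 0.4 × 3/√2 = 0.849 SD.

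The documents give neither k nor δ. The ranges below are assumptions.

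| k | δ = 0.25 SD | δ = 1.0 SD | Share of 0.849 SD |
|---|---|---|---|
| 2 | 0.0125 | 0.05 | 1.5% to 5.9% |
| 4 | 0.025 | 0.10 | 2.9% to 11.8% |
| 6 | 0.0375 | 0.15 | 4.4% to 17.7% |

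The shift moves a contrast between arms to the extent that it differs between them. Its sign is that of δ, which is unknown.

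**The case against.** The strongest reply is that 4.3 is one summary sentence in a condensed article. It follows text on good clinical practice and on recording severity, so a sensible physician would read it as harm that warrants stopping, which is close to 4.4(7) and (9). The article also uses trial, study and treatment loosely, so leaving the study need not mean forgoing the 3-month sample. Retention after discontinuation is often set out in a full protocol that is not shown. Finally, k and δ are assumed, the exercise is of moderate intensity and led by a physiotherapist, and k = 6 would spend the whole allowance of one arm on harm alone.

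Part of this stands. The contrast between treatment and study is not clean, because the lead sentence of 4.4 blurs it. The size of any bias is unknown and its direction is not established. The lack-of-effect trigger in the same sentence of 4.3 is the more serious one, because it depends on outcome, and correcting the harm clause does not deal with it.

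The rest does not remove the point. The softer reading is not in the text: the rule is mandatory, is triggered by any harm and acts on study participation. The follow-up kept in 4.3 is for safety, and no other section shown keeps the efficacy sample. The point therefore concerns a stated rule, not detail that a condensed article leaves out.

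**Conclusion.** The concern holds. Followed as written, 4.3 is wider than 4.4(7) and (9), and it forfeits the hormonal primary outcome of any woman removed for harm before month 3. The reason for loss can be related to treatment.

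The sample size is correct and power is barely touched. The plausible cost is a shift in an arm's mean change of about 0.01 to 0.15 SD, for an assumed 2 to 6 removals and an assumed difference of 0.25 to 1.0 SD between retained and removed women. No number of removals is claimed, and an excess in Arm C is an inference. The change should be made because the text conflict is plain, the lost sample cannot be recovered and the correction is cheap. Confidence in the practical importance is medium.

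**What to change.** In Section 4.3, replace removal from the study for harm with discontinuation of the affected trial treatment (exercise, walking or supplement) under the criteria already in 4.4(7) and (9). Add that adverse-event follow-up and the scheduled 3-month assessment, including AMH and FSH, continue unless the participant withdraws consent.

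This takes one or two sentences. It adds no visit or test, because Table 1 already contains the 3-month assessment. Participants stay protected, because a treatment that is harming a woman is still stopped.

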## 2. Experimental Design

This protocol was written in accordance with the Standard Protocol Items: Recommendations for Interventional Trials (SPIRIT) reporting template [30]. This was a single-center, randomized (1:1:1), open-label clinical trial, with three treatment groups: per os therapy (Group A), per os therapy and walking (Group B), per os therapy and special exercise (Group C). The purpose of randomization is to eliminate selection bias. The study protocol was approved and registered by the Human Reproduction Committee of Hungarian Medical Research Council (25489-8/2021/EÜIG).

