#### 2.3.1. Primary Outcome

The primary outcome is the change in FSH and AMH levels compared with the levels before. Spontaneous pregnancy during the study period will be recorded as a primary outcome measure.

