### 2.4. Sample Size

A parallel, 3-group design will be used. We determined the sample size using G*Power 3.1.9.7 software. We employed one-way analysis of variance (ANOVA) due to consideration of three different therapies. The effect size was estimated at 0.4. We set alpha to 0.05 and power to 0.95. Consequently, the software provided an estimated total sample size of 102, resulting in 34 cases per group. To account for a potential dropout rate of 15%, we increased the sample size to 40 participants per group. Therefore, the total sample size needed for the study is 120 participants [31].

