## 4. Detailed Procedures

### 4.1. Intervention

The standard dietary supplement/vitamin oral therapy for all three groups includes the intake of a preparation containing myo-inositol + folic acid orally twice a day. Participants in the study are asked to take 3 mg of melatonin before bedtime in addition to daily intake of 1000 mg of vitamin C (slow release), 400 mg of vitamin E, 2500 IU/day of vitamin D3, and 200 mg of Coenzyme Q10.

Combined with the supplement therapy, patients in Arm B will be asked to perform low intensity walking 3 times per week for 1 h each session.

For Arm C (per os therapy and special exercise), our special 70 min moderate-intensity exercise program is available 3 times a week for at least 3 months. This therapeutic exercise program is designed to combine several professional aspects in all exercises including postural correction, pelvic-lumbar stabilization, rehabilitation of the pelvic region, re-education of the pelvic floor muscles, restoration of optimal diaphragm function, dynamic mobilization and stretching exercises, use of the relaxation and therapeutic effects of costo-diaphragmatic breathing, optimization of joint range of motion, and development of balance and coordination. There is a large emphasis on the combination of exercises with relaxation-type exercises of costo-diaphragmatic breathing. The constant attention on breathing helps the patients relax, activates the parasympathetic nervous system, and ensures the strengthening of multiple muscle groups by contraction and relaxation.

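### Removal from the study for ineffectiveness, and an attendance cut-off for Arm C alone, can lose 3-month hormone outcomes on grounds that may relate to response

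*Protocol article*

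**What the plan says.** Two rules in the protocol article matter here.

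- **Section 4.3.** If the monitoring physician sees harm or "signs of ineffectiveness during the trial, the participant will be removed from the study". The text speaks of the study, not of treatment. It applies to a participant in any arm and gives no measure or threshold of ineffectiveness.
- **Section 4.4, criterion 5.** One ground for discontinuation is "attendance of fewer than 75% of the exercise sessions by the participant in the intervention group". Arm B also has three sessions a week (Section 4.1: "patients in Arm B will be asked to perform low intensity walking 3 times per week for 1 h each session") but no attendance threshold. Arms A and B fall only under criterion 4, "failure to adhere to the study rules", which is not quantified.

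Section 4.4 is unclear about what its list governs. The heading speaks of trial treatment, while the opening sentence reads "The criteria for the discontinuation of a trial are as follows".

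Four other places bear on this:

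- Section 2: "This was a single-center, randomized (1:1:1), open-label clinical trial, with three treatment groups".
- Section 2.3.1: "The primary outcome is the change in FSH and AMH levels compared with the levels before", with spontaneous pregnancy also primary.
- Table 1: AMH and FSH are drawn at baseline and at 3 months, with nothing between.
- Section 2.5: baseline is compared with 3 months within each group by paired tests, and the three groups are compared by ANOVA or Kruskal–Wallis.

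No section says that a woman who is removed or discontinued still attends the 3-month visit.

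**The concern.** Sections 2 and 4.2 give the elimination of selection bias as the purpose of randomisation. A rule that takes women out afterwards because treatment seems not to work selects on something close to the outcome. A rule that takes out poor attenders in one arm filters that arm differently from its comparators.

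Since the primary hormone outcome exists only at 3 months, a woman who leaves before then has no AMH or FSH change. An analysis plan written later can say that all randomised women are analysed, but it cannot supply blood samples that were never drawn. That is why the point belongs in the protocol text. What is at stake is the within-arm improvement claims and the comparison of Arm C with Arms A and B.

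**Working it through.** **1. The plan's own figure.** Section 2.4 uses one-way ANOVA with k = 3, f = 0.4, alpha = 0.05 and power 0.95. The noncentrality is f²N, which is 0.16 × 102 = 16.32 at N = 102. Noncentral-F power is 0.949 at N = 99 and 0.955 at N = 102, so 102 (34 per group) is the smallest balanced size that reaches 0.95. For 15% dropout, 102 / 0.85 = 120, or 40 per group. Both stated figures reproduce. If all 120 women are analysed, power at f = 0.4 is 0.979.

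**2. The attendance rule (Arm C only).** The documents give neither the share removed, q, nor the correlation, rho, between the removal score and the outcome. Both are assumptions here. If the lowest share q on the score is removed, the expected shift of the remaining Arm C mean, in SD units, is

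shift = rho × phi(c) / (1 − q), where c is the standard normal q-quantile and phi its density.

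phi(c) / (1 − q) is 0.274 at q = 15%, 0.424 at 25% and 0.570 at 35%. Multiplying by rho gives the shifts below. The false-positive rates come from 20,000 simulated trials per row with no true effect, 40 women per arm, and 6, 10 or 14 women removed from Arm C only.

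| q | rho | Shift of Arm C (SD) | C better than A (nominal 2.5%) | Three-arm ANOVA (nominal 5%) |
|---|---|---|---|---|
| 15% | 0.3 | 0.08 | 5.2% | 6.2% |
| 25% | 0.3 | 0.13 | 7.2% | 7.6% |
| 35% | 0.3 | 0.17 | 10.0% | 9.8% |
| 15% | 0.5 | 0.14 | 8.6% | 8.4% |
| 25% | 0.5 | 0.21 | 14.5% | 12.9% |
| 35% | 0.5 | 0.28 | 19.9% | 18.0% |

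At rho = 0 the shift is zero and both rates stay at about their nominal values.

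**3. The ineffectiveness rule (all arms).** If it is applied equally and there is no true effect, every arm shifts alike and the expected difference between arms is zero. The within-arm tests are still affected. As an outer bound, suppose exactly the worst responders in an arm of 40 are removed (rho = 1). Removing 5%, 10% or 15% shifts the mean change by 0.11, 0.19 or 0.27 SD. The paired test then falsely shows improvement in 11.5%, 27.6% or 47.0% of trials, against a nominal 2.5%. The real effect should be smaller, because no interim AMH or FSH is scheduled. Under Section 4.7 only the menstrual cycle is followed throughout. Its length is a secondary outcome.

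**The case against.** Much of the opposing case stands, and it limits the point.

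- **The ineffectiveness rule is not specific to an arm.** A reader might infer that it favours Arm C directly. The text does not support that. A difference between arms arises only if unmasked physicians apply the rule unequally. Figures that assume outcome-based removal from Arm C alone do not describe this rule.
- **There is no interim AMH or FSH.** The scheduled tests give the physician no hormone values on which to select, so removal exactly on the outcome is a bound and not an expectation.
- **Section 4.4 may mean stopping treatment only.** Its heading says so, and its list includes spontaneous pregnancy, which is itself a primary outcome. Meeting a criterion therefore cannot by itself mean exclusion from analysis. This makes reconciliation necessary, but it does not soften Section 4.3, which says removal from the study.
- **No completer analysis is stated.** Section 2.4 inflates the groups with the words "To account for a potential dropout rate of 15" per cent. A reader might infer that removed women are counted as dropouts, left out of the analysis, and use up the allowance by design. The article says none of this and gives no removal rate. Naming the analysis set is commonly left to the analysis plan, and its absence is not the point here.
- **Poor attendance is not poor response.** Criterion 4 covers all arms, Arm A has no sessions to attend, and bias needs a link between attendance and outcome that the documents do not quantify.

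What the objection does not answer is that a stated rule ends participation on grounds that may relate to response, and no text preserves the 3-month measurement.

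**Conclusion.** The point holds as a conditional risk created by stated rules. Section 4.3 takes women out of the study on an undefined, response-related ground judged by an unmasked physician. Section 4.4 sets a numerical attendance criterion for one arm, under a heading and a sentence that conflict. With no provision for continued follow-up, the primary hormone outcome of these women is lost.

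For the attendance rule, the illustration gives a shift of 0.08 to 0.28 SD and a false-positive rate for C over A of 5.2% to 19.9%, against 2.5%. This covers assumed removal of 15% to 35% and correlations of 0.3 to 0.5. At zero correlation there is no bias. For the ineffectiveness rule, the main exposure is the within-arm tests.

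It would go too far to say that randomisation is broken or that bias toward Arm C is certain. The loss cannot be repaired after the fact, and preventing it is cheap, so the text should be changed.

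**What to change.** 1. In Sections 4.3 and 4.4, separate stopping trial treatment, which stays with the clinicians, from leaving the study. Reconcile the heading of 4.4 with its opening sentence.
2. Do not use ineffectiveness or low attendance as grounds for leaving the study.
3. Collect the scheduled 3-month outcomes on all randomised women unless consent is withdrawn. Where pregnancy occurs, record it as the outcome and handle the hormone values by a stated rule, since the early-cycle sample cannot then be taken.
4. Analyse women in their assigned arm.
5. Use the 75% attendance figure only to define a supportive per-protocol set, with comparable adherence reporting for Arm B.

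The cost is protocol wording and an already scheduled 3-month visit for women who stop treatment. The planned sample size does not change. The estimated difference between C and A may turn out smaller.
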